##### Supportive censoring scheme:

Patients will be censored at the earliest of: outcome of interest, death date, 'transferred out date', 'last collection date', 5 years after the index date, or the derived last date of study drug. By censoring around the time of last study drug this scheme should include only events likely to be due to the drug taken.

#### **o Primary outcome**

The primary efficacy endpoint will be the time to first occurrence of confirmed stroke (ischemic, hemorrhagic, or of unspecified type), or systemic embolism during the study, regardless of whether the subject is receiving treatment at the time of the event (i.e. using the primary censoring scheme).

Comparisons will be made according to prescribed treatment (apixaban vs warfarin) for time to stroke/SE.

This analysis approach will be used as the primary analysis for all 3 objectives.

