## L. Definition of the Study population

For all objectives two datasets of UK primary care data will be combined: CPRD Gold and CPRD Aurum. Patients with a prescription for an oral anticoagulant in the time period 01 January 2013 to 31 January 2019 (exact cut-off date dependent on date of final data extracts) and a prior diagnosis of atrial fibrillation will be selected as the EHR cohort. Apixaban gained UK marketing authorisation in January 2013 for the indication of prevention of stroke and systemic embolism in AF patients; the minimum date is set to capture all patients prescribed apixaban for this indication in the UK. A previous study validated the use of diagnostic read codes for identifying patients with AF in CPRD by sending surveys to GPs and found a confirmation rate of 98% among patients originally identified with AF codes.

### Objective 1

**Step 1:** We will select all (HES and ONS linked) patients in the EHR cohort who would have met the following eligibility criteria for inclusion in the ARISTOTLE study, at least 6 months after patient registration in an up to standard practice: or 6 months post-UTS date, whichever is later:

- a diagnosis of AF,
- age over 18 years,
- at least one of the following risk factors for stroke: diagnosis of congestive heart failure, hypertension requiring pharmacological treatment, age greater than 75, diabetes mellitus, and prior stroke or systemic embolism,
- no AF due to reversible causes (e.g. thyrotoxicosis, pericarditis),
- no clinically significant (moderate or severe) mitral stenosis, in EHRs clinical significance and severity are not consistently recorded therefore a diagnosis of mitral stenosis will be sufficient to exclude a patient,
- no increased bleeding risk that is believed to be a contraindication to oral anticoagulation (e.g. previous intracranial haemorrhage),
- no conditions other than AF that require chronic anticoagulation (e.g. prosthetic mechanical heart valve),
- no persistent, uncontrolled hypertension (systolic BP > 180 mm Hg, or diastolic BP > 100 mm Hg), in EHRs this will be implemented by excluding patients whose latest blood pressure reading in the 6 months prior to the index date is over the systolic or diastolic blood pressure limit
- no active infective endocarditis,
- no concomitant treatment with aspirin > 165 mg/day,
- no simultaneous treatment with both aspirin and a thienopyridine (e.g., clopidogrel, ticlopidine),

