- no severe comorbid condition with life expectancy of  $\leq 1$  year,
- no active alcohol or drug abuse, or significant psychosocial difficulties (e.g., psychosis, dementia),
- no recent ischemic stroke (within 7 days),
- no severe renal insufficiency (serum creatinine > 2.5 mg/dL or a calculated creatinine clearance < 25 mL/min),
- no ALT or AST > 2X ULN or a Total Bilirubin  $\geq 1.5$ X ULN (unless an alternative causative factor such as Gilbert's syndrome is identified),
- no platelet count  $\leq 100,000/\text{mm}^3$ ,
- no haemoglobin < 9 g/dL,
- no prior exposure to apixaban,
- no women who are pregnant or breastfeeding

For the 3 criteria involving patient laboratory results (renal insufficiency, low platelet count, and low haemoglobin) a patient will be excluded if their last test result in the 90 days prior to the index date meets the exclusion criteria.

**Step 2:** Next we will determine if/when these patients received apixaban or warfarin. Individuals in EHR who have more than one warfarin eligibility period within their record will be able to contribute more than once to the pool of warfarin subjects (with the covariates and person-time contributed unique to the specific eligibility period) as long as they have no past apixaban exposure.

**Step 3:** Having obtained individual level patient data for ARISTOTLE participants from Bristol Myers-Squibb we will then match each ARISTOTLE apixaban participant 1:1 with the closest available apixaban patient record in our EHR pool. We will consider matching on a selection of the following ARISTOTLE baseline characteristics:

- age
- sex
- body mass index
- systolic blood pressure (mmHg)
- history of congestive heart failure or left ventricular systolic dysfunction

[figure not shown]

- hypertension requiring pharmacological treatment
- diabetes mellitus
- prior stroke or TIA or thromboembolism
- smoking status [current smoker, former smoker, or never smoked]
- alcohol consumption [none, low, moderate, heavy]
- renal impairment [severe, moderate, mild, normal based on the CrCL value]
- prior VKA/warfarin use
- concomitant treatment with:
  - anticoagulant/VKA use other than warfarin or apixaban
  - aspirin
  - antiplatelets
  - NSAIDs
  - lipid lowering drug therapy
  - CYP3A4 inhibitors

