##### Treatment Switching and Discontinuation

[figure not shown]

As the primary analysis accounts neither for treatment switching nor for treatment discontinuation and does not capture that these may be unfavourable outcomes both the proportion of patients discontinuing treatment and time to treatment discontinuation will be tabulated by prescribed treatment.

o Regression model

Hazard ratio (apixaban/warfarin) comparing the event rate (%/yr).

Interpretation: This estimand targets the treatment-policy effect of treatment initiation of apixaban vs initiation or continuation of warfarin on the time to first stroke or systemic embolism.

All time to event endpoints will be analysed using a Cox proportional hazards model including treatment group as a covariate and prior warfarin/VKA status (experienced, naïve).

Point estimates and two-sided 95% CIs for HR will be constructed for the outcome.

o Validation of Observational Results Against Aristotle Data

In Objective 1 alone we will validate the findings from our primary analysis against ARISTOTLE by determining whether results of the EHR analysis are compatible with the ARISTOTLE trial results. The ARISTOTLE trial demonstrated superiority of apixaban over warfarin for the primary endpoint (HR 0.79, 95% CI 0.66-0.95). The treatment effect seen with the EHR data may be weaker than that seen in ARISTOTLE.

A subgroup analysis looking at the outcomes of the EU patients in ARISTOTLE showed a smaller treatment difference with the estimate for HR below 1 but upper limit of the CI crossing 1 for the primary efficacy endpoint and death: HR for stroke/SE = 0.92 (95% CI = 0.56; 1.52), HR for all cause death = 0.89 (95% CI = 0.68; 1.18). It was suggested in the European Medicines Agency (EMA) Assessment Report that the smaller treatment effect seen in the EU patients could be due to better INR control in the warfarin arm of the EU subgroup (median TTR 68.93%). This study could provide additional evidence on this point. Since all the patients in our cohort are from the UK the results can be compared with the results from the ARISTOTLE patients in the EU.

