##### **Missing Prescription Data**

Treatment may be initiated in secondary care meaning the first prescription of patients newly initiating treatment is missing. To account for these potentially missing first prescriptions we will perform a sensitivity analysis where those newly initiating treatment are assumed to have a missing earlier prescription and therefore assigned an earlier derived index date. Patients who are hospitalised may also have prescriptions issued in secondary care leading to treatment gaps seen in their primary care prescription data. The primary analysis using the Prescribed Population will not be affected by such gaps as patient time is included until the patient is censored or experiences an event regardless of treatment gaps. The supplementary analysis using the On-treatment Population and the safety analysis censor at derived date of last dose and may therefore miss events whilst a patient was on treatment in hospital. We will investigate the occurrence of hospitalisation around treatment discontinuation and assess the potential impact on the results of such missed events by performing a sensitivity analysis with different extended derived dates of last dose (extending the final period to 60 or 90 days after the final prescription estimated end).

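### Patients can enter from day 8 after an ischaemic stroke, but no stated rule separates a new stroke from a repeat record of the old one, and the listed between-arm covariates ignore how recent the prior stroke was.

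*Protocol*

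**What the plan says.** Section O (Primary outcome) defines the endpoint as "time to first occurrence of confirmed stroke (ischemic, hemorrhagic, or of unspecified type), or systemic embolism during the study". It does not say how a stroke is confirmed.

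Section L, Objective 1, Step 1 lists, among the risk factors that qualify a patient, "diabetes mellitus, and prior stroke or systemic embolism". The only limit on the timing of a pre-index stroke is "no recent ischemic stroke (within 7 days". Previous intracranial haemorrhage is a separate exclusion example, so the question mainly concerns ischaemic and unspecified strokes. Section E describes Objective 3 as having no entry criterion beyond AF, and Section O applies the same primary analysis to it.

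Section O (Index date) sets index at the first relevant prescription on or after the date the patient first met eligibility. Section Q adds that "Treatment may be initiated in secondary care meaning the first prescription of patients newly initiating treatment is missing".

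The matching list in Section L, Step 3 opens with "We will consider matching on a selection of the following ARISTOTLE baseline characteristics". It includes "prior stroke or TIA or thromboembolism" and "prior VKA/warfarin use", neither with a time element. Step 4 carries the list into the between-arm matching and allows further EHR variables. Section O states the estimand as the "treatment-policy effect of treatment initiation of apixaban vs initiation or continuation of warfarin", and the Cox model adjusts for prior warfarin/VKA status.

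**The concern.** In routine records, a stroke code dated after index need not be a new stroke. It may be a discharge letter entered late, a follow-up code or a readmission for the same event. This is most likely when index falls soon after a stroke, and the plan permits that from day 8.

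The rules on outcome recording do not cover this. Section N treats an absent record as no event, and Section Q (Missing Outcome Data) deals with missed events. The earlier-index sensitivity analysis in Section Q moves index back for new initiators, which can bring the old stroke closer to index or place it after index.

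A recent stroke can prompt starting or switching treatment, whereas continuing warfarin needs no such prompt. Two matched patients may both have a stroke history, one from last month and one from years ago, and the listed covariates would call them alike. The primary HR then carries events that say nothing about the drugs. Objective 1 judges that HR against a fixed window, and the Technical Summary makes the extension to under-represented patients conditional on replicating the trial.

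**Working it through.** **What the plan gives.** About 9,000 patients per arm, so 2 × 9,000 = 18,000, which agrees with Section L. The benchmark is HR 0.79 (95% CI 0.66 to 0.95). The criteria in Section O are an HR between 0.69 and 0.99 and an upper 95% limit below 1.52, with superiority if the upper limit is below 1. The plan states no event rate, event count or power, no frequency of repeat stroke records, and no distribution of recent strokes by arm.

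**Illustration 1: more repeats on apixaban.** Assumptions, none from the documents:
- 1.5 stroke/SE per 100 patient-years on warfarin, 2 years' follow-up, true HR 0.79
- 1% to 3% of apixaban patients indexed soon after a stroke
- 5% to 20% of those strokes re-recorded after index
- warfarin arm with 25% to 50% as many repeat records

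True events: warfarin 9,000 × 0.015 × 2 = 270; apixaban 0.79 × 270 = 213.3. SE(log HR) = √(1/213.3 + 1/270) = 0.0916, giving a CI of 0.66 to 0.95, so the assumed information is close to that of the trial.

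Repeat apixaban records: 9,000 × 0.01 × 0.05 = 4.5 up to 9,000 × 0.03 × 0.20 = 54. HR is approximated by the event ratio at equal person-time:
- low end: (213.3 + 4.5)/(270 + 2.25) = 0.80
- high end: (213.3 + 54)/(270 + 13.5) = 267.3/283.5 = 0.94; SE = √(1/267.3 + 1/283.5) = 0.0853; upper limit 0.943 × exp(1.96 × 0.0853) ≈ 1.11

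Superiority is lost with about 17 repeat records on apixaban and 4 on warfarin: 230.3/274.25 = 0.84, upper limit 1.00. Seventeen is 0.2% of 9,000. With half as many on warfarin, about 24 and 12 are needed.

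Allowing for sampling error, the chance that the estimate exceeds 0.99 rises from 0.7% (z = ln(0.99/0.79)/0.0916 = 2.46) to 28% at the high end (z = ln(0.99/0.943)/0.0853 = 0.57).

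**Illustration 2: the split varied.** From the benchmark interval, SE = ln(0.95/0.66)/3.92 = 0.0929. Solving 1/d_a + 1/d_w = SE² with d_a = 0.79 d_w gives about 207 apixaban and 262 warfarin events. Now assume 90 repeat records in total (0.5% of 18,000):

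| Split apixaban:warfarin | HR |
|---|---|
| 30:70 | (207.3 + 27)/(262.5 + 63) = 0.72 |
| 50:50 | (207.3 + 45)/(262.5 + 45) = 0.82 |
| 70:30 | (207.3 + 63)/(262.5 + 27) = 0.93 |
| 90:10 | (207.3 + 81)/(262.5 + 9) = 1.06 |

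An equal split only pulls the HR toward 1, reaching 0.84 at 1% (180 records). The split determines the direction and most of the size.

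**The case against.** **Code-level definitions may sit elsewhere.** Acute versus history codes, HES diagnosis position and washout windows often belong in an analysis plan or codelists. The appendix also points to the group's papers for outcomes used here. The endpoint says confirmed stroke, and linkage to HES inpatient data is planned to improve ascertainment. This largely stands. A reader might infer that any stroke record counts, but the text does not say so; it leaves confirmation undefined. The covariate list is different, because the protocol sets it out itself and timing is absent. It is open to additions, so adding recency completes the list and corrects no misstatement.

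**Repeat records need not fall mostly on apixaban.** A reader might infer that they do from the contrast of initiation with continuation. The documents do not show it. A stroke can itself make a warfarin continuer eligible, with index soon after day 7. Step 2 of Section L lets warfarin patients contribute several eligibility periods, and one could open just after a stroke. Matching or adjusting for prior VKA use, where done, brings naive starters in both arms closer together. Hospital initiation is described only as possible, Section O says AF prescribing is predominantly through GPs, and nothing confines hospital initiation to apixaban. This stands as to direction. It does not remove the possibility of imbalance, since prior VKA status does not equalise time since stroke: a VKA-experienced apixaban patient is a switcher, and the matched warfarin patient may be a stable continuer.

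**The 7-day limit copies the trial.** That is so, and the limit is not criticised here.

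**Conclusion.** The point holds in a limited form. Repeat records of a pre-index stroke can be counted as primary events, and the stated covariates would not correct a difference between arms in how recent those strokes were. A higher share on apixaban is plausible but not shown, and the bias could run in either direction.

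A reader might infer that this would make the validation fail. The first illustration does not support that: the expected HR of 0.80 to 0.94 stays inside the window, and the worst-case upper limit of about 1.11 is well below 1.52. Expected failure needs a more extreme assumption, such as 90 repeat records split 90:10. Loss of superiority is the nearer risk. Section O accepts non-inferiority as compatible with the trial, so the validation would survive. However, the protocol uses superiority to judge whether the result resembles the whole trial or its EU subgroup, and that reading could change.

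Confidence in the size is low, because every rate driving it is assumed. The change is still worth making, because it is cheap and protects the primary HR.

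**What to change.** 1. In Section L, Step 4, add time since last stroke/TIA (for example ≤90 days, >90 days, none) to the between-arm matching or propensity score covariates.
2. In Section O, state that only incident stroke/SE counts: a HES admission with acute stroke/SE as primary diagnosis and an admission date after index, or an ONS stroke death. Do not count history or follow-up codes, or a GP-only code within a fixed window (for example 30 days) after an earlier stroke record. Apply the rule identically in both arms and to Objective 3. Because it relies on linkage, reconcile Section L, Step 1, which selects linked patients, with Section Q, which makes the linked cohort a sensitivity analysis.
3. Repeat the primary analysis excluding patients with a stroke in the 30 days before index. This also covers readmissions for the old stroke that pass the rule in item 2.

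The cost is codelist and programming work on data already requested. A few true early recurrences recorded only by the GP would be lost, and the matched sample may be slightly smaller.

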#### **o Descriptive analyses**

##### Demographic and Baseline Characteristics

Frequency distribution and summary statistics for demographic and baseline variables will be presented by treatment group for the EHR patients, both before and after matching steps.

##### Treatment Switching and Discontinuation

[figure not shown]

As the primary analysis accounts neither for treatment switching nor for treatment discontinuation and does not capture that these may be unfavourable outcomes both the proportion of patients discontinuing treatment and time to treatment discontinuation will be tabulated by prescribed treatment.

o Regression model

Hazard ratio (apixaban/warfarin) comparing the event rate (%/yr).

Interpretation: This estimand targets the treatment-policy effect of treatment initiation of apixaban vs initiation or continuation of warfarin on the time to first stroke or systemic embolism.

All time to event endpoints will be analysed using a Cox proportional hazards model including treatment group as a covariate and prior warfarin/VKA status (experienced, naïve).

Point estimates and two-sided 95% CIs for HR will be constructed for the outcome.

o Validation of Observational Results Against Aristotle Data

In Objective 1 alone we will validate the findings from our primary analysis against ARISTOTLE by determining whether results of the EHR analysis are compatible with the ARISTOTLE trial results. The ARISTOTLE trial demonstrated superiority of apixaban over warfarin for the primary endpoint (HR 0.79, 95% CI 0.66-0.95). The treatment effect seen with the EHR data may be weaker than that seen in ARISTOTLE.

A subgroup analysis looking at the outcomes of the EU patients in ARISTOTLE showed a smaller treatment difference with the estimate for HR below 1 but upper limit of the CI crossing 1 for the primary efficacy endpoint and death: HR for stroke/SE = 0.92 (95% CI = 0.56; 1.52), HR for all cause death = 0.89 (95% CI = 0.68; 1.18). It was suggested in the European Medicines Agency (EMA) Assessment Report that the smaller treatment effect seen in the EU patients could be due to better INR control in the warfarin arm of the EU subgroup (median TTR 68.93%). This study could provide additional evidence on this point. Since all the patients in our cohort are from the UK the results can be compared with the results from the ARISTOTLE patients in the EU.

By assessing superiority and non-inferiority we will see whether the treatment effect observed is more similar to the study results as a whole (apixaban superior) or the EU subgroup results. Either a result of superiority or non-inferiority will be considered compatible with the ARISTOTLE trial results. We have set two criteria that must be met for us to conclude results are consistent with the result demonstrated in the trial:

1. The effect size must be clinically comparable with the ARISTOTLE findings; the hazard ratio for time to stroke/systemic embolism with the EHR must be between 0.69 and 0.99. This range is not symmetrical around the ARISTOTLE estimate of 0.79 as it is anticipated that the treatment effect in routine clinical care may be weaker than that seen in the optimised setting of a clinical trial.

2. The upper limit of the 95% confidence interval for the rate ratio must be less than 1.52 (upper limit in the EU subgroup of ARISTOTLE).

In addition, if the upper limit of the 95% CI is less than 1 then superiority of apixaban vs warfarin will be concluded. Either result (superiority or non-inferiority) will be taken as evidence that EHR data may be useful to look at NOACs

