#### **o Censoring**

##### Index date

The index date for the EHR cohort will be the date of the patient's first prescription of apixaban or warfarin (for objectives 1 and 2), or for objective 3 first prescription of apixaban, warfarin, rivaroxaban, or dabigatran on or after the date the patient first met the eligibility criteria for the trial in the treatment period of interest

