### Sensitivity analyses

All primary and secondary efficacy outcomes described above (stroke/SE combined and individually, MI, and mortality) will also be analysed using the supportive censoring scheme described above in which patients are censored around the time of last study drug. This analysis targets the effect of initiation of apixaban vs initiation or continuation of warfarin on the time to event while on prescribed treatment and investigates whether the extent of treatment discontinuation compromises confidence in the primary and secondary efficacy analyses.

The exclusion of patient-time post initially prescribed treatment discontinuation in the safety and sensitivity analyses might bias the results towards a conclusion of no difference, for example if those at higher bleeding risk were more likely to discontinue one of the treatment arms due to minor bleeding events than if those same minor

[figure not shown]

bleeding events occurred with the other treatment. The set of patients who switch or discontinue treatment during the study period will be examined to ascertain whether biases of this nature have occurred. The proportion of patients switching or discontinuing treatment, timings of withdrawal, and their baseline characteristics will be summarised by initially prescribed treatment.

Additional analyses may be performed using methods such as inverse-probability-of-censoring weighting or a rank-preserving structural failure time model to estimate the treatment effect that would have been observed in the absence of treatment switching.

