We expect different adherence in routine clinical practice compared with the trial adherence may explain some of the difference in treatment effect observed between routine clinical care and the trial. Adherence will therefore be estimated in the EHR cohort to enable comparisons with the trial and investigate the extent to which this may have influenced differences in treatment effect. With the EHR data we do not know how many tablets a patient has taken or if a given prescription is filled by a patient. We will estimate the proportion of time covered by prescribing as a proxy measure for adherence; this proxy measure assumes that all prescriptions are filled and that a patient takes all tablets in the prescription. This measure of adherence is not expected to accurately estimate the adherence of a given individual but should give an idea of how adherent a patient is compared with others. Prescribing for AF in the UK is predominantly through GPs meaning prescribing information from other potential sources of treatment should not be missing. However, it is possible that a patient's first prescription may be issued in hospital and treatment prescribed during any periods of hospitalisation will not be recorded in a patient's EHR leading to missing exposure data.

We will calculate the proportion of days covered (PDC) over a patient's time when on prescribed treatment as a measure of adherence. PDC will be estimated using patient prescription data including the total number of tablets prescribed, daily dose, and number of days on treatment (derived date of last dose – index date +1). This method of estimating adherence cannot easily be used for warfarin due to daily dose being poorly recorded in EHR; in a sample of CPRD Gold warfarin prescription records many patients had dose recorded with noninformative text such as “take as directed”. Depending on the quality of the prescription data warfarin adherence may instead be estimated by looking at patient adherence to other long-term daily medications as a proxy for warfarin adherence; the reliability of this measure would then be explored by comparing this proxy measure in the apixaban users with the PDC calculated directly using the apixaban prescription data.

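### Discontinuation is tabulated by drug alone, although warfarin patients may be continuing users while apixaban patients enter at first use, so the arms differ in time since start of drug

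*Protocol*

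**What the plan says.** Among the descriptive analyses in section O, under Treatment Switching and Discontinuation, the protocol states that "both the proportion of patients discontinuing treatment and time to treatment discontinuation will be tabulated by prescribed treatment". The reason given is that the primary analysis ignores switching and stopping and does not reflect that either may be a bad outcome for the patient.

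A second summary appears in section O under Sensitivity analyses: "The proportion of patients switching or discontinuing treatment, timings of withdrawal, and their baseline characteristics will be summarised by initially prescribed treatment". Its purpose is to see whether unequal stopping has biased the safety and on-treatment results. Major bleeding, the key safety outcome, is analysed with censoring around the last dose.

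The following text settles who enters each arm and when:

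- The estimand in section O (Regression model) contrasts "treatment initiation of apixaban vs initiation or continuation of warfarin".
- The Objective 1 criteria in section L require "no prior exposure to apixaban". They do not bar past warfarin, and a patient may supply several warfarin eligibility periods.
- The index date in section O is the first relevant prescription "on or after the date the patient first met the eligibility criteria for the trial in the treatment period of interest". For warfarin this need not be the patient's first ever.
- The study window in section L opens with UK authorisation of apixaban in AF: "the minimum date is set to capture all patients prescribed apixaban for this indication in the UK".
- The adherence calculation under Sensitivity analyses counts days on treatment from the index date. The discontinuation paragraph itself names no origin.

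**The concern.** A table of stopping by drug invites the reader to compare the drugs. Here one column holds only people on their first prescription of the drug. The other mixes new starters with people who may have taken warfarin for years and have already shown that they persist with it. If stopping is concentrated early, the mixed column will show less and later stopping even when the drugs are equally well tolerated.

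This is not a matter of unequal follow-up. A Kaplan-Meier estimate at a fixed time would show the same gap, because it is the time origins that differ.

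Two uses are at stake. The first table is where stopping and switching are put on view as possible unfavourable outcomes. The second summary is the check for differential stopping behind the major bleeding and on-treatment analyses. In both, a gap due to continuing users could be taken for a difference between drugs.

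**Working it through.** The protocol states no discontinuation rate, so there is no figure of its own to reproduce. The check has two parts.

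**Do the planned safeguards align time on drug?**

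1. Prior VKA/warfarin use is a candidate matching variable (section L, Steps 3 and 4). It records history, not duration. Even with exact matching, a VKA-experienced apixaban patient is on day 0 of the drug, while the matched warfarin patient may be years into it.
2. Prior VKA status (experienced or naïve) is a term in the Cox model. That adjusts the endpoint hazard ratios and does not touch a descriptive table.
3. The earlier derived index date in section Q (Missing Prescription Data) applies only to new initiators, to recover a missed first prescription.

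None of these reaches the discontinuation table.

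**How large could the gap be?** All inputs below are assumptions: both drugs share one stopping pattern by time since first use, and time in the table runs from the index date.

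*Two-level hazard.* Assume 0.4 per year in the first six months and 0.1 per year afterwards, with continuing users past the first six months.

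- Starters at one year: 1 − exp(−(0.5 × 0.4 + 0.5 × 0.1)) = 1 − exp(−0.25) = 22.1%.
- Continuing users at one year: 1 − exp(−0.1) = 9.5%.
- Warfarin arm with share c continuing: (1 − c) × 22.1% + c × 9.5%, which gives 18.3%, 15.8% and 13.3% for c = 0.3, 0.5 and 0.7. The apixaban arm shows 22.1% throughout.
- With an early hazard of 0.3: starters 1 − exp(−0.2) = 18.1%; warfarin arm at c = 0.5, 13.8%.

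*Weibull pattern, as a check on the shape.* S(t) = exp(−λt^k), with λ set so that 30% of new users stop by one year. A share f = 60% of the warfarin arm enters after d = 3 years on the drug, with persistence S(t + 3)/S(3). At k = 0.5, continuing users stop at 1 − exp(−0.357 × (2 − 1.732)) = 9.1% in the first year, so the warfarin arm shows 0.4 × 30.0% + 0.6 × 9.1% = 17.5%.

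| Hazard over time | k | Apixaban, 1 year | Warfarin, 1 year |
|---|---|---|---|
| Falling steeply | 0.5 | 30.0% | 17.5% |
| Falling | 0.7 | 30.0% | 21.5% |
| Constant | 1.0 | 30.0% | 30.0% |
| Rising | 1.3 | 30.0% | 41.4% |

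At k = 0.5 with d = 3 years, warfarin at one year ranges from 23.7% (f = 30%) to 11.2% (f = 90%). At f = 60%, the time until a quarter have stopped is 0.65 years on apixaban and 1.90 years on warfarin. If the comparison is limited to new starters of each drug (f = 0), the arms coincide at 30.0% for every k.

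**The case against.** The strongest reply is that this is a descriptive table with no decision attached. The validation criteria rest on the stroke/systemic embolism hazard ratio and its confidence interval, and the bleeding and on-treatment estimates are computed without the table. Extra columns could be left to an SAP. The protocol is also open about contrasting initiation with initiation or continuation, and the planned baseline summary of patients who stop could reveal an imbalance in VKA experience.

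Much of that stands: no effect estimate changes. But the protocol itself fixes the layout twice, by drug alone, and gives the tables an interpretive purpose. A baseline summary would show VKA history at most, not time already on the drug.

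A second objection concerns the summary under Sensitivity analyses, and it succeeds. The question there is who is actually censored in the analysed arms. If continuing warfarin users stop less often than apixaban starters, that is real differential censoring, not a display artefact. A reader might infer that this summary should be confined to VKA-naïve patients. The document does not support that, since such a subset would not describe the people being censored.

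A reader might also infer that the table is bound to make apixaban look worse. That needs a stopping hazard that falls with time on drug. The protocol gives no hazards and no share of continuing users, and a rising hazard would reverse the gap.

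**Conclusion.** The point holds in conditional form. The stated layout mixes new and continuing users in the warfarin column only, so it cannot separate a difference between drugs from a difference in time since start of drug. The size is unknown. Under the two-level assumptions the spurious gap at one year runs from about 4 points (22.1% against 18.3%) to about 9 points (22.1% against 13.3%). It is zero under a constant hazard.

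The conclusion rests on three things. The index date as time origin is inferred from the index-date definition and the adherence formula; it is the only origin that the protocol offers. First use of apixaban is explicit for Objective 1 and only implied, by the opening of the study window, for Objectives 2 and 3. The direction depends on the shape of the stopping hazard.

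Nothing here bears on the primary hazard ratio, and nothing in the protocol says that the table will be used to rank the drugs on tolerability. It is worth changing because the change is cheap and the table is otherwise hard to interpret.

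**What to change.** In section O, Treatment Switching and Discontinuation:

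- State the time origin for time to discontinuation.
- Present discontinuation and switching separately by prior VKA status.
- Draw the between-drug comparison from VKA-naïve initiators of each drug.
- Label the VKA-experienced columns as not comparable on time since start of drug.

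In section O, Sensitivity analyses, keep the by-arm summary of the whole analysed cohort and add the same VKA-naïve/experienced split. A difference due to continuing users can then be told apart from a difference between drugs.

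The cost is a change of table layout and a sentence or two of text, since prior VKA status is already needed for the Cox model. The drawback is that the direct comparison rests on fewer patients.
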